## Methods

### Design

A two-armed RCT will be conducted to compare the intervention condition (IC) ICare Stimmung with a wait-list control group (WLC). Individuals assigned to the WLC will receive access to the intervention 6 months after study begin. They can contact the study administration at any time through the messaging function on the platform or by email. They can seek other treatment after study uptake and they additionally receive an information sheet detailing psychological treatment options upon high symptom severity assessed in the diagnostic interview or upon contacting the study administration team.

Diagnostic interviews and self-report assessments will take place at baseline (T1), post-assessment (T2), and at 6-month follow-up (T3) (see Figure 1 for a detailed overview). There will also be weekly mood assessments during the first 7 weeks of the study phase. Diagnostic interviews will be conducted via telephone. Self-report data will be collected using a secure online-based assessment system (AES, 256-bit encrypted). All procedures involved in the study will be consistent with the generally accepted standards of ethical practice. The study was approved by the Friedrich-Alexander-Universität Erlangen-Nürnberg ethics committee (No. 144_16B). The trial is registered in the German Clinical Trial Registry under DRKS00011690 (https://www.drks.de/drks_web/).

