### Assessments

Clinician-based and self-report assessments will take place at screening (T0), baseline (T1), post-assessment 8 weeks after randomization (T2), 6-month follow-up (T3), and 12-month follow-up in the IC group (T4). There will also be weekly mood assessments during the first seven weeks of the study phase. See Figure 1 for a detailed overview of the study flow and Table 2 for an overview of all assessments. Clinician-based diagnostic assessments will be conducted via telephone.

**Table 2 T2:** Overview of self-report assessments.

**Construct**	**Questionnaire**	**T0**	**T1**	**T2**	**T3**
Demographics	Socio-demographic data (SozDemo)	✓	–	–	–

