#### Primary outcome

The primary outcome will be clinician-based ratings of depressive symptom severity at post-assessment (T2). Clinician-rated depressive symptom severity will be assessed by the QIDS-C (53) which covers nine criteria with 16 items: sleep, sad mood, appetite/weight, concentration/decision making, self view, thoughts of death or suicide, general interest, energy level, and restlessness/agitation. The items are each rated from 0 to 3. A meta-analysis found Cronbach's alpha to be acceptable to good (α = 0.69 − 0.89) (54). Trained psychologists' who are blind to treatment condition will conduct the diagnostic interviews. Interrater reliability will be examined by rating interviews a second time of ~10% of participants by a second rater. Several measures will be taken to ensure blinding: (1) explaining to the participant the importance of keeping the interviewers blinded to randomization status, (2) verbal reminder before each assessment, (3) documentation after each assessment whether the assessor is still blind to study condition.

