#### Clinical analyses

Data analysis will be performed on an intention-to-treat (ITT) basis. Additionally, per protocol analysis including only participants who have completed the primary outcome will be analyzed. Missing data will be handled by multiple imputations (MI) with 100 iterative estimations per value, as this is currently regarded as the gold standard with regard to missing data (100). Demographic variables as well as other baseline variables will be inserted into the prediction model to estimate missing values. Differences in the primary and secondary outcomes between the two study groups will be examined with repeated measurements analysis of variance, and standardized effect sizes (Cohen's *d*) and number needed to treat (NNT) and their respective confidence intervals will be calculated for comparison. Response and remission rates will be compared across groups with contingency tables and differences tested with χ2. All unidirectional hypotheses will be tested one-sided, bidirectional hypotheses will be tested two-sided. Alpha is set to *p* < 0.05. All analyses will be conducted with SPSS.

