#### Power and sample size calculation

We expect superiority of the IC compared to the WLC in the primary outcome, clinician-based depression symptom severity at post-assessment. The most recent systematic review on internet-based interventions for MDD found a standardized mean difference of *g* = −0.90, 95% CI −1.07 to −0.73 between the ICs compared to untreated controls (27). We based the sample size calculation on the lower bound of the 95% confidence interval. To demonstrate standardized effect sizes, Cohens *d*, of 0.73 with a power (1 – β) of 80% and an alpha of 0.05 in a one-sided test (calculated using G^*^Power) 48 individuals would need to be included in total (24 per group). As we aim to also explore moderators of treatment outcome, and as simulation studies show that the sample size required to detect an interaction effect of the same magnitude as in the primary analysis needs to be about three to fourfold (101), we will include *N* = 200 participants. This sample allows to detect effect sizes of *d* = 0.35 in the primary endpoint analysis.

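### The primary endpoint is QIDS-C at T2, but the stated repeated-measures ANOVA is not tied to T2; a baseline-adjusted T2 comparison (ANCOVA) would be, and is more precise at almost no cost

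*Protocol article*

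**What the plan says.** The Primary outcome section fixes one measure at one time: "The primary outcome will be clinician-based ratings of depressive symptom severity at post-assessment (T2". The Power and sample size calculation section repeats that the expected superiority concerns post-assessment.

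The only test given for continuous outcomes is in Clinical analyses, in one sentence that serves primary and secondary outcomes alike: "Differences in the primary and secondary outcomes between the two study groups will be examined with repeated measurements analysis of variance". Baseline variables are named there for the imputation model, and elsewhere as moderators. They are not named as covariates of the primary comparison.

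Both arms are assessed on three occasions. From the Design section: "Diagnostic interviews and self-report assessments will take place at baseline (T1), post-assessment (T2), and at 6-month follow-up (T3". The 12-month assessment is for the intervention arm only.

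The sample size assumes d = 0.73 with power "of 80% and an alpha of 0.05 in a one-sided test", which gives 24 per group. For N = 200 the article adds: "This sample allows to detect effect sizes of *d* = 0.35 in the primary endpoint analysis". The rule on sidedness is: "All unidirectional hypotheses will be tested one-sided, bidirectional hypotheses will be tested two-sided".

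**The concern.** A repeated-measures ANOVA with two groups offers several tests: a group main effect, a group-by-time interaction over two occasions, or an interaction over three. They answer different questions and have different power. All of them fit the sentence in Clinical analyses, but only some concern the T2 difference that the article calls primary.

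Two things are at stake. The first is the target: under some of these tests a significant primary result need not say anything about T2. The second is precision: under the reading that does target T2, the test discards information that a baseline-adjusted comparison would use. The detectable effect of 0.35, which the article assigns to the primary endpoint analysis, may then not belong to the analysis that is run.

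**Working it through.** **Inputs.** From the article: d = 0.73, one-sided alpha 0.05, power 80%, 24 per group, N = 200 at 1:1 (100 per arm), detectable d = 0.35, and shared occasions T1, T2 and T3. Not in the article, so assumed: T1-T2 correlation r of 0.3, 0.5 and 0.7; the ratio k of T1 SD to T2 SD (1, or 0.7 as an alternative); no dropout; and compound symmetry where three occasions enter.

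**Step 1: the article's own figures.** For a one-sided two-sample t-test (noncentral t), 24 per arm at d = 0.73 gives power 80.1%. At 100 per arm the effect detectable with 80% power is 0.353, and power at d = 0.35 is 79.4%. Both stated figures reproduce as a plain two-group comparison of T2 scores. Two-sided, the figures would be 31 per arm and 0.398.

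**Step 2: T1-T2 group-by-time.** This term equals the t-test on T2 minus T1. Relative to the T2-only comparison, the variance factors are:

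- change score: 1 + k² − 2kr, which is 2(1 − r) when k = 1
- ANCOVA on T1: 1 − r²

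Their difference is (k − r)², so ANCOVA is never worse, apart from one degree of freedom. With k = 1 the ratio is 2(1 − r)/(1 − r²) = 2/(1 + r). Detectable d is 0.353 times the square root of the factor.

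| r (k = 1) | Change factor | ANCOVA factor | Ratio | Detectable d, change | Detectable d, ANCOVA | Power at d = 0.35, change | Power at d = 0.35, ANCOVA |
|---|---|---|---|---|---|---|---|
| 0.3 | 1.40 | 0.91 | 1.54 | 0.417 | 0.337 | 67.0% | 82.7% |
| 0.5 | 1.00 | 0.75 | 1.33 | 0.353 | 0.306 | 79.4% | 88.6% |
| 0.7 | 0.60 | 0.51 | 1.18 | 0.273 | 0.252 | 93.8% | 96.5% |

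All entries are one-sided. A simulation of 3,000 runs per correlation agreed.

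With k = 0.7 and r = 0.3 the change factor is 1 + 0.49 − 0.42 = 1.07. The ratio is 1.07/0.91 = 1.18, and the detectable d is 0.353 × √1.07 = 0.365.

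**Step 3: when 0.35 carries over.** The change score does at least as well as the T2-only comparison when 1 + k² − 2kr ≤ 1, that is when r ≥ k/2. This means r ≥ 0.5 for k = 1 and r ≥ 0.35 for k = 0.7.

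**Step 4: the other readings.**

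- *T1-T2 group main effect.* It averages in a pre-randomization score, so the true effect is halved. One-sided power at d = 0.35 is 45%, 41% and 38% for r = 0.3, 0.5 and 0.7 (k = 1).
- *T1-T2-T3 group-by-time.* This is an F test on 2 and 396 df with noncentrality (n/2) Σ(δ_t − mean)²/(1 − r), n = 100. Take no effect at T2 and d = 0.35 at T3. The centred effects are −0.117, −0.117 and 0.233, with sum of squares 0.0817. At r = 0.3 the noncentrality is 50 × 0.0817/0.7 = 5.83, and the test rejects 57% of the time. At r = 0.5 and 0.7 it rejects 72% and 92%. An F test on 2 df has no one-sided form.

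**Step 5: the planning effect.** At d = 0.73 and N = 200, the T1-T2 interaction and ANCOVA both exceed 99% power at all three correlations (k = 1).

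**The case against.** The strongest reply has four parts.

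- **The natural reading targets T2.** With the endpoint fixed at T2, T1-T2 group-by-time is the obvious meaning. Under randomization that term is unbiased for the T2 difference. It has 1 df, so it can be tested one-sided as the article requires. This stands. A reader might infer that the planned ANOVA cannot isolate T2 or cannot be one-sided; that is true of the three-occasion interaction, but not of this term. The article nowhere says that T3 enters the primary test, so that reading is a possibility and not a stated plan.
- **An article leaves such detail to the full protocol or SAP.** This stands in part: a missing list of occasions would not be a finding alone. But the article does state a method, and it assigns a detectable effect to the primary analysis that reproduces for a different test.
- **The size of the loss is assumed.** The article gives no correlation or SDs. A reader might infer a 54% penalty because everyone enters with MDD, which restricts the T1 range and lowers r. The same restriction shrinks the T1 SD. With a T1 SD of 0.7 of the T2 SD the penalty at r = 0.3 is about 18%, and the detectable d of 0.365 is close to the stated figure.
- **The trial is not underpowered.** N was raised from 48 to 200 for moderators, and at d = 0.73 power is above 99% by either method. This stands; the loss matters only near d = 0.35.

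**Conclusion.** The point holds as an improvement in precision and in alignment with the endpoint. It is not an error that threatens the primary result. As written, the test is not tied to T2, and tests with different targets all comply with it.

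Under the reading most favourable to the plan, the analysis is valid but less efficient than ANCOVA. With equal SDs its variance is larger by 54%, 33% and 18% at r = 0.3, 0.5 and 0.7; with a T1 SD of 0.7 of the T2 SD the excess at r = 0.3 is about 18%. A reader might infer that the stated 0.35 is simply wrong for the planned analysis. The documents do not support that: with equal SDs it carries over to the T1-T2 interaction when r is about 0.5 or more, and fails below that (about 0.42 at r = 0.3, against 0.34 for ANCOVA).

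No bias is shown for the T1-T2 term. These sizes rest on assumed correlations and SDs and on no dropout; the three-occasion figures also assume compound symmetry.

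**What to change.** - State the primary analysis as an ANCOVA: QIDS-C at T2 regressed on arm and T1 QIDS-C in each imputed data set, with the arm coefficient pooled by Rubin's rules. A mixed model with a prespecified T2 contrast would also serve. Either allows the one-sided test that the sample size assumes.
- State explicitly that QIDS-C is rated at T1. The article implies this through its baseline clinician-based assessments but does not say so.
- Analyse T3 separately, as secondary.
- Say that d = 0.35 refers to an unadjusted one-sided comparison of T2 scores, or restate it for the ANCOVA with the assumed correlation.

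The cost is a few sentences. No extra participants are needed and, provided QIDS-C is rated at T1 as implied, no new data.

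### Remission (QIDS-C ≤6) is tested with an unadjusted χ2 although the baseline QIDS-C is available: a valid test that gives up some power

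*Protocol article*

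**What the plan says.** The Clinical analyses section of the protocol article fixes the method for the two binary outcomes: "Response and remission rates will be compared across groups with contingency tables and differences tested with χ2". No covariate is named. The same section sets the surrounding rules: "All unidirectional hypotheses will be tested one-sided, bidirectional hypotheses will be tested two-sided", "Alpha is set to *p* < 0.05" and "Missing data will be handled by multiple imputations (MI) with 100 iterative estimations per value". It also promises an NNT with a confidence interval.

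The Secondary outcomes section defines remission as a QIDS-C score of 6 or lower, and response as a 50% symptom reduction on the CES-D or the GAD-7. Both are secondary.

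The Design and Assessments sections place diagnostic interviews and clinician-based assessments at T1. Table 2 lists self-report instruments only, so it does not show the QIDS-C. A T1 QIDS-C is nevertheless implied by the planned repeated-measures analysis of the primary outcome. Randomisation is 1:1 in blocks of 8, with no stratification by severity described.

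**The concern.** An absolute cut-off asks little of someone who enters just above it and a great deal of someone who enters with a high score. Baseline severity should therefore predict remission. The article itself lists MDD severity among its a priori predictors and moderators of outcome.

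Neither the randomisation nor the χ2 uses that information. The variation in remission that baseline severity explains is left as noise, so the comparison is less sensitive than the collected data allow. At stake is precision: a lower chance of detecting a real difference in remission, and a less precise risk difference behind any NNT. The validity of the randomised comparison is not at stake.

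**Working it through.** **Inputs from the article.** N = 200 at 1:1, so 100 per arm; alpha 0.05; remission at QIDS-C ≤6; unadjusted χ2. **Assumed, because the article gives neither:** the remission rates, and the correlation r between the baseline and end scores.

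**1. The plan's own sample-size figures.** These concern the primary outcome. The inputs are an effect "of 0.73 with a power (1 – β) of 80% and an alpha of 0.05 in a one-sided test". Normal approximation: n per group = 2(1.645 + 0.842)²/0.73² = 12.37/0.533 = 23.2, so 24 per group and 48 in total, as stated. With 100 per arm the detectable d is 2.487 × √(2/100) = 0.352, which agrees with "This sample allows to detect effect sizes of *d* = 0.35 in the primary endpoint analysis". Neither figure is affected by this point.

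**2. Power of the planned χ2, for 20% against 35%.** Mean rate 0.275.
- SE under the null = √(2 × 0.275 × 0.725/100) = 0.0631.
- SE under the alternative = √(0.2 × 0.8/100 + 0.35 × 0.65/100) = 0.0623.
- Two-sided power = Φ[(0.15 − 1.96 × 0.0631)/0.0623] = Φ(0.42) = 66.3%.

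**3. Effect of adding baseline.** Simulated trials with 100 per arm. Baseline x is standard normal, the end score is r·x + √(1 − r²)·e, and remission means the end score falls below an arm-specific threshold. The χ2 is compared with the likelihood-ratio test for arm in a logistic model with arm and x, both two-sided at 5%. In the first two scenarios the cut is −0.85 SD with a latent shift of 0.35 or 0.45, so the rates are Φ(−0.85) = 19.8% against Φ(−0.50) = 30.9% or Φ(−0.40) = 34.5%.

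| Remission | r | χ2 | Adjusted | Gain (points) |
|---|---|---|---|---|
| 20% vs 31% | 0.4 | 45.6% | 49.8% | 4.2 |
| 20% vs 31% | 0.5 | 43.1% | 49.3% | 6.2 |
| 20% vs 31% | 0.6 | 44.3% | 53.5% | 9.2 |
| 20% vs 34% | 0.4 | 68.4% | 71.7% | 3.3 |
| 20% vs 34% | 0.5 | 65.6% | 73.2% | 7.6 |
| 20% vs 34% | 0.6 | 64.6% | 75.2% | 10.6 |
| 20% vs 35% | 0.3 | 66.4% | 69.1% | 2.7 |
| 20% vs 35% | 0.5 | 66.1% | 73.8% | 7.7 |
| 30% vs 45% | 0.3 | 59.3% | 61.2% | 1.9 |
| 30% vs 45% | 0.5 | 58.6% | 66.8% | 8.2 |
| 20% vs 40% | 0.3 | 89.8% | 91.6% | 1.8 |
| 20% vs 40% | 0.5 | 87.2% | 92.2% | 5.0 |

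The first six rows use 2,000 trials each and the rest 4,000. The χ2 power does not depend on r, so its spread within one pair of rates is simulation noise (standard error about 1 point or less). At r = 0.7 the gain would be 8 to 17 points. I would not lean on that, because everyone must have MDD at entry, which narrows the baseline range and may lower r.

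**4. Validity.** With 20% in both arms, two-sided rejection rates were 4.8–5.3% for the χ2 and 4.6–5.0% for the adjusted test.

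**5. Response.** A 50% reduction was simulated on a CES-D-like scale: baseline mean 28, SD 8, floored at 16; control end mean 22, SD 10; d = 0.45 (all assumed). Power, χ2 to adjusted: 70.2% to 70.7% (r = 0.3), 73.3% to 73.3% (0.4), 78.2% to 79.1% (0.5), 79.8% to 81.3% (0.6). The gain is 0 to 1.5 points.

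**The case against.** The strongest reply is that this is a conventional, valid test on a secondary outcome for which the trial was not sized. The repeated-measures analysis already uses baseline for the continuous scores behind these dichotomies. Chance imbalance in severity is covered by the test's error rate, so it bears on precision and does not cause bias. The gain depends on a correlation the article does not give, and at 0.3 it is small. All of this stands, and it limits the point to efficiency.

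Three stronger readings are tempting, and the article does not support them.

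- *The χ2 contradicts a one-sided rule.* The rule is conditional: "All unidirectional hypotheses will be tested one-sided, bidirectional hypotheses will be tested two-sided". The only direction stated is for the primary outcome. A χ2 on 1 degree of freedom is also the square of z, so it can be run one-sided through its signed root. For 35/100 against 22/100, χ2 = 4.147 and p = 0.0417; the one-sided p is half of that, 0.0209. At most, the sidedness for remission and response is not spelled out, and an analysis plan may settle it.
- *The χ2 cannot be used with multiple imputation.* The 2×2 table yields a risk difference with a standard error, which pools by Rubin's rules, and there are methods for combining χ2 statistics. A log odds ratio from the adjusted model pools directly, which is convenient but does not show the plan to be in error.
- *Response ignores baseline in the same way.* Each participant's own baseline score is in the definition, and the remission power figures do not carry over.

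**Conclusion.** The point holds for remission, as a loss of efficiency in a valid secondary analysis. With 100 per arm and remission of 20% against about 31–35%, the χ2 gives up about 2–3 points of power at a correlation of 0.3, 6–8 at 0.5 and 9–11 at 0.6. Over all the rates tried, the loss is about 2–3 points at 0.3 and 5–8 at 0.5. These figures rest on assumed rates and correlations and on a normal latent-score model. They ignore dropout and imputation. Nothing here touches type I error, the primary analysis or the sample size. Because the better analysis uses data already collected, the change is worth making, but it is an improvement and does not correct an error.

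**What to change.** Make the main remission comparison a logistic regression on arm plus T1 QIDS-C. Fit it in each imputed data set and pool the log odds ratio. From the same model, report the standardised (marginal) risk difference with its confidence interval and take the NNT from it. The marginal risk difference is needed because the adjusted odds ratio is conditional on baseline and does not translate directly into an NNT. Keep the crude contingency table as description.

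For response, the same model with the T1 score of the scale concerned (CES-D or GAD-7) may be used for consistency, without expecting much power from it. It would also help to state in the same place whether these tests are one- or two-sided.

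The cost is a sentence or two in the analysis section and some extra programming for the standardised risk difference and its pooled interval. No additional data are needed. The article already plans regressions with arm and baseline terms for the moderator analyses. The change should be fixed before outcome data are seen by arm.

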#### Power and sample size calculation

We expect superiority of the IC compared to the WLC in the primary outcome, clinician-based depression symptom severity at post-assessment. The most recent systematic review on internet-based interventions for MDD found a standardized mean difference of *g* = −0.90, 95% CI −1.07 to −0.73 between the ICs compared to untreated controls (27). We based the sample size calculation on the lower bound of the 95% confidence interval. To demonstrate standardized effect sizes, Cohens *d*, of 0.73 with a power (1 – β) of 80% and an alpha of 0.05 in a one-sided test (calculated using G^*^Power) 48 individuals would need to be included in total (24 per group). As we aim to also explore moderators of treatment outcome, and as simulation studies show that the sample size required to detect an interaction effect of the same magnitude as in the primary analysis needs to be about three to fourfold (101), we will include *N* = 200 participants. This sample allows to detect effect sizes of *d* = 0.35 in the primary endpoint analysis.

#### Predictor and moderator analyses

Predictors and moderators of treatment outcome will be analyzed on an exploratory basis with a priori defined potential moderators: sociodemographic factors such as gender, age, income, education, ethnicity, socioeconomic status, education level, status of employment, relationship status, sexual orientation, religious, and spiritual orientation, current and previous mental health including age of MDD onset, MDD severity, low energy, number of previous episodes, duration of episodes, MDD chronicity, concurrent antidepressant use, current/past suicidality, suicide attempts, comorbid anxiety, anxiety sensitivity, substance use, perceived stress, insomnia/sleep problems, rumination, need for affect, sense of mastery, self-esteem, resilience, self-regulation, quality of life, experience with psychotherapy, physical health including diet, weight, body mass index, body satisfaction, number of medical conditions, physical functioning, sedentary behavior, smoking, drug use, quality of life, life events including childhood maltreatment/trauma, and life events, minority, and perceived social status, discrimination, experience of abuse, parental and familial psychopathology, social environment, social support/relationships, relationship satisfaction, loneliness, personality traits such as neuroticism and openness to experiences, and psychological coping skills such as emotion regulation skills. Regression analyses will be used to test interaction effects between baseline moderators and the intervention condition, using the SPSS macro PROCESS (102). Significant interactions will further be investigated applying the Johnson-Neyman technique to detect the region of significance (103).

